### Outcomes

Primary outcome: a global neurodevelopment evaluation will be obtained at 12 to 18 months corrected age for all patients to compare the effect of early systematic intervention independently of formal enriched environments in motor and cognitive aspects. The infants will be evaluated in relation to their motor, and cognitive neurodevelopment using AIMS and Bayley III scales between 12 and 18 months corrected age [14–16].

AIMS (Alberta motor infant scale): a blinded physiotherapist will evaluate the children of both groups between 12 and 18 months with Alberta Infant Motor (AIMS) scale in all eligible patients. The evaluation will be conducted in the presence of parents or caregivers in a safe surface with room for the child move around during the evaluation. The examiner will interact with the child to encourage response, but physical facilitation of movement should be avoided. During the evaluation, they are punctuated behaviors more or less mature within the motor repertoire of the child in each position (supine, prone, sitting and standing). This repertoire is called “motor” window. All items priced within the window motor and the window motor to the previous items are scored. The evaluation of the end, the child will receive a score based on the sum of the items scored on each posture, called raw score. This score will be observed in a standardized chart to find the baby development percentile according to the chronological age or corrected. Percentiles instrument standards are: 5%, 10%, 25%, 50%, 75%. According to this percentile baby’s development can be classified into three categories: normal or typical (percentile> 25%), suspicious (percentile> 5% and ≤ 25%), abnormal or atypical (percentil≤5%) [14].

BSDI-III: *Bayley scales of infant and toddler development third edition*: The Bayley Scales of Infant and Toddler Development, Third Edition, will be used for assessment of neurodevelopment at 12 and 18 months’ corrected age. The scales will be administered at the hospital clinic, on the same day of each follow-up visit, by a psychologist who was blinded to group allocation. Cognitive, motor, and language development will be considered normal if higher than 89; below average if 80 to 89; borderline if 70 to 79; and extremely low if less or equal 69. Examine all the facets of a young child’s development according manual [15].

AIMS and Bayley Scales are recommended to use together and in different ages because false positives are common and therefore it is beneficial to follow-up children at high risk of motor impairment at more than one time point, or to use a combination of assessment tools [8].

Secondary outcome: We have evaluated parental stress and parental infant bonding at hospital discharge in all preterm infants included in the study and survival in the neonatal period.

PARENTAL BONDING INSTRUMENT (PBI) had been applied by a professional blind to the group to which the child belongs. These questionnaires are to be used for research purposes only. PBI is a self-administered Likert scale (0 to 3) instrument, with 25 questions related to father and mother, in which subjects answer how similar those behaviors were to their parents’ behavior until the age of 16 years. The instrument measures two constructs: the first one is affection, which is more consistent and clearly bipolar (affection, heat, availability, care, sensitiveness versus coldness and rejection); the second construct is control or protection (control, intrusion versus encouragement of autonomy) [20].

Emotional availability scales –EAS: this scale will be used to assess both groups at the end of the study. The EAS consists of six scales; four scales assess adult emotions and behavior related to sensitivity, structuring, non-intrusiveness, and non-hostility. The other two scales are related to child behavior. Child responsiveness to the caregiver assess the child interactions with the adult; and child involvement with the caregiver scale assesses the behaviors regarding to child invitations to caregiver to join her in the play and the interaction talks with the caregiver. The scales scores are obtained by scores measured in each dimension using a Likert-type continuous scale with scores between 1 and 7.

Other outcomes: Nutritional conditions during hospital stay and follow up program. Prevalence rates of exclusive breastfeeding and mixed feeding at 6 months corrected age will be recorded to measure maternal bond, in both groups. Anthropometric measures are plotted according to gender and corrected age using the WHO curves. Growth velocity has been registered in the reference curves, using two computers with an appropriate statistical program for nutritional assessment (ANTHRO). There is a nutritionist of the multidisciplinary group that makes home visits and other nutritionist to perform the growth evaluations in the exact moments in each group (blinded to which group the child was previously allocated).

The study protocol has used the SPIRIT 2013 checklist, so we are presenting the participant timeline [23] (Fig. 1):Multidisciplinary team training meetings (20 sessions/1 h each): All the team will need to be trained to teach the tactile-kinesthetic stimulation by mothers. They are modules of guidelines for the entire multidisciplinary team.Identification of eligible subjects.Written informed consent is read and signed by the parentsA researcher have done a randomization method for subjects allocation (48 h after birth)Intervention group (tactile-kinesthetic stimulation by mothers) or conventional care is begun according randomization in the 7th day of life in neonatal unit until hospital discharge.All preterm infants and their mothers are followed during neonatal period.Multidisciplinary team prepares all eligible patients for hospital discharge, promotes regular meeting with the mothers, and high standard guidance for all patients, followed by two groups of care according to the previous randomization.Parental stress and parental infant bonding at hospital discharge in all preterm infants included in the study and survival in the neonatal period is evaluated.All patients are referral to follow up program ten days after discharge.Both arms are referral to monthly follow-up visits until 6 months of corrected age; bimonthly up to 12 months CA; and each 3 months until 24 months CA in both groups.Intervention Group receives ten additional appointments for systematic orientation for a continuous global simulation at home.Following each additional appointment, the multidisciplinary team has does home visits to check and answer mother’s doubts regarding of the stimulation’s program.Neurodevelopment Outcome measure at 12–18 months CA in all patients (both arms) by blinded professional.

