Ophthalmologist	Evaluation of Retinopathy of Prematurity (ROP), visual acuity, strabismus
Ear, nose and throat doctor	Evaluation and management of hearing problems
Nutritionist	Management of growth failure
Speech Therapist	Speech problems and swallowing problems
Nurse	Immunization and Hygiene control

During the appointments, feeding orientations, weight gain, general health/illness and infections are recorded. A 24 h dietary recall is administered at each visit to assess feeding routines, use of formula, breast milk, and family food preferences. Routinely feeding orientations have been offered according their needs (exclusive breastfeeding or mixed feeding or infant formula; nutritional requirements according their corrected age). Recurrent admissions during the first year of life, anthropometric parameters (weight, head circumference, body mass index, and length at 6, 12 and 18 months of corrected age (z scores plotted on WHO growth charts), and results of routine tests performed at 1 year of corrected of age are systematically recorded.

Patients will have their motor neurodevelopment evaluated by AIMS (Alberta Infant Motor Scale at 6 and 12 moths of CA) and forwarding to specialized professionals according to their necessity. The scale was translated and adapted to the Portuguese language, being quick and easy to application. The reliability and reproducibility showed satisfactory values [14]. Applications of the Bayley Scales, cognition, language and motor (BSDI- III, Bayley Scale Development Index, version III), by qualified and trained professional will be performed at 12 months CA for all infants [15].

The examiner is able to distinguish, by means of comprehensive and standardized protocols for neurological development, developmental scales and tests between the normal biological variation and the deviant development. The clinical approach has the great advantage of being easily repeated, obtaining developmental trajectories that can lead to neurological disorders being suspected in both arms [16] .

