Follow up appointments, home visits, intervention during follow up program and all systematic orientation for early intervention have been done according to developmental milestones, anticipating in a month evolutionary step acquisition of motor and/or cognitive expected for corrected age. The theoretical neurodevelopmentalist referential of the main periods for the acquisition of developmental landmarks have been used [22].

During the sessions the patient should be well fed, have slept his nap and comfortable. Parents are learning to read your preterm’s behavior and respect their needs. We have distributed flyers with techniques and science-based activities to be applied systematically and sequentially at home. Parents have one flyer per appointment; a total of 10 flyers with orientations will be distributed for each subject of IG. Each patient will have a complete book of orientations in the end of the study.

In IG, during first six months corrected age, mother, father and / or corresponding caregivers have been received six flyers: simple guidelines to encourage large motor skills, fine and cognition and some toys.

From discharge up to three months corrected age: Sitting next to their children parents must place them on their stomach on the floor, being sure that their face, mouth, and nose is not covered, using a foam roller to position. Although tummy time is very important, preterm infants should also have time playing on their backs; so stimulation is also performed with the child in the position lying in bed or prone position and/or during bath; a number of three detailed guideline orientations is offered for each included family. Folders with detailed illustrations are offered to parents:

Gross and fine motor stimulation: Crossing arms and relaxation movements (play in the bath for 5 to 10 min, beating hands and feet in water, rubber animals). To make gymnastic movements with flexion and passive extension of the upper and lower limbs; in order to support themselves on the upper limbs in the prone position and to acquire the expected rolling ability.

Cognitive stimulation: Getting close and speak slowly, singing low. Use a mobile to look up, black and white gloves to put in the hands’ mother to play and the child turn your head 180 °C.

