Gross and fine motor stimulation: gymnastics intends to tone the muscles in order to prepare for the first sitting position and then standing without support, to walk independent. Using a large plastic ball (the ball should not be too full) the mother is oriented to hold the child against him, one hand holding his knees thereof and the other the chest. Using the floor with EVA material for the child to have displacement space, the parents play small colored balls twice a week talking about the game (action/reaction). To stimulate fine motor, is guided to offer magazines to be torn by the child, showing how to do it quietly. Once torn into several pieces, teach to make a paper ball with the pieces and play ball with the child.

Cognitive stimulation: In the mirror, mother shows different colored pieces (balls, books) talking slowly each color and numbers, using gestures when she talks to child, linking her actions to her words**.**

From 8 months of corrected age, display and nominate the body parts: head, belly, hand, foot, mouth, nose, eyes. Read books and show the animal pictures, repeating the name of each figure well paused and with the mouth wide open. Material kit for the seventh and eighthappointments: Small colored balls of non-toxic rubber (number = 6). EVA Material (100 cm × 100 cm).Toy fit, action/reaction toy, colored cubes with all geometric forms (one for each subject included in IG).

From 13 up to 18 months corrected age: study protocol has two detailed guidelines and appointments. Parents have been learned to speak and to teach the child mimics what other people do, babbling syllables like words, demonstrating what she wants with gestures; they need to encourage the child to get physically involved with the toy to strengthen muscles and confidence.

Gross and fine motor stimulation: reinforced by the researchers that the game and the play are the best way to stimulate a child. Using a large plastic ball, the mother/father is oriented to tilt the child’s chest to the ball until he/she can put the hands to make a little effort to get up; following the stimulation, the child learns to roll the ball, causing the release of both hands. It is important to advise the mother to release the child gradually hip.

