Evaluate the impact of the intervention in the neurodevelopment of the children	More strengthened ties to the program start, as measured by PBI resulting in higher scores of attention, care and protection . Number of patients with the Bayley III scale normal for corrected age Number of patients with AIMS scale normal for corrected age. Statistical measures of the differences between the groups (intervention and conventional approaches).	At discharge of neonatal unit (PBI) we will have the first evaluation. After 10 sessions and home visits we will have the follow up evaluations. AIMS and Bayley III Scales at 12 to 18 months corrected age A global neurodevelopment evaluation will be obtained at 12 to 18 months corrected age for all patients.

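### The age of the primary assessment is stated inconsistently, and a 12-month test cannot come after all ten sessions as Table 2 requires

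*Protocol article*

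**What the plan says.** The primary outcome paragraph (Protocol article, Outcomes) states that "a global neurodevelopment evaluation will be obtained at 12 to 18 months corrected age for all patients". For the AIMS, the same section says that "a blinded physiotherapist will evaluate the children of both groups between 12 and 18 months". For the Bayley-III, it says that the scales "will be used for assessment of neurodevelopment at 12 and 18 months’ corrected age", given in the hospital clinic on follow-up visit days by a psychologist blinded to allocation.

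The description of follow-up under Conventional group (Methods) says that the Bayley scales "will be performed at 12 months CA for all infants", and places AIMS at 6 and 12 months.

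Table 2, Objective 3, gives an order instead of an age: "After 10 sessions and home visits we will have the follow up evaluations". It then repeats the 12 to 18 month range.

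The programme itself runs past 12 months. The intervention description says: "From 13 up to 18 months corrected age: study protocol has two detailed guidelines and appointments". The materials list identifies these as the ninth and tenth appointments. Each appointment is followed by a home visit, and Methods (Interventions) requires all ten of each to be completed.

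For AIMS, the examiner is to "find the baby development percentile according to the chronological age or corrected", whereas Table 2 counts infants who are normal for corrected age.

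**The concern.** These statements concern the primary endpoint and cannot all hold. A 12-month score reflects an unfinished programme. An 18-month score can reflect all of it. A score at any age in between reflects a part that varies from infant to infant. With both a 12- and an 18-month Bayley and no ranking between them, the primary time point could be settled after results are known.

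The Table 2 order also raises a question of comparability. Control infants have no sessions to complete. If completion decides when an intervention infant is tested, that infant cannot be tested before 13 months, while a control can be tested at 12.

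The AIMS wording adds a smaller ambiguity. The classification cuts at the 5th and 25th percentiles, and the age used to read the percentile can move an infant across a cut.

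**Working it through.** **1. Session count.** Methods lists the orientation sessions by corrected age. For discharge to 3 months, "a number of three detailed guideline orientations is offered for each included family". There are three more at 3 to 6 months, two at 7 to 12 months and two at 13 to 18 months.

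- Total: 3 + 3 + 2 + 2 = 10, which reproduces the stated ten appointments.
- Due by 12 months: 3 + 3 + 2 = 8, so at most 8/10 = 80%.
- Due at 13 to 18 months: 2/10 = 20%.

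**2. The timing statements side by side.**

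| Place | Timing | Can all ten sessions be complete? |
|---|---|---|
| Methods, Conventional group | Bayley at 12 months, all infants | No, at most 8 |
| Outcomes, Bayley | 12 and 18 months | Not at 12; possible at 18 |
| Outcomes, primary and AIMS | Anywhere from 12 to 18 months | Depends on the infant |
| Table 2, Objective 3 | After ten sessions and visits, at 12 to 18 months | Yes, but then not at 12 months |

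**3. How many intervention infants would be tested early.** The document does not give the age at session 10 or the distribution of test ages. Assume test age is uniform over 12 to 18 months and session 10 is at age T. The share tested before session 10 is (T − 12)/6:

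- T = 13: 17%
- T = 15: 50%
- T = 18: 100%

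If Table 2 were strictly enforced, the share would be 0%. If all were tested at 12 months, it would be 100%. The document therefore does not fix this quantity.

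**4. Illustrative power.** The sample size section gives 84 patients, 5% significance, 80% power and a 3-point difference, but no SD. Assume a two-sided two-sample t-test with 42 per arm.

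- Back-solved effect: d = 0.619 SD. The noncentrality is 0.619 × √(42/2) = 2.84, and power is 80%, as stated.
- Suppose a fraction q of the benefit comes from the neonatal unit phase, the rest accrues in proportion to sessions, and every infant is tested at 12 months. The share of benefit retained is q + (1 − q) × 0.8.

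| q (assumed) | Share retained | Effect (SD) | Power |
|---|---|---|---|
| 0 | 0.80 | 0.495 | 61% |
| 0.25 | 0.85 | 0.526 | 66% |
| 0.50 | 0.90 | 0.557 | 71% |

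**5. AIMS reference age.** Counting correction from 40 weeks, the gap between chronological and corrected age is (40 − gestational age) × 7/30.44 months:

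- 31.9 weeks: 1.9 months
- 28 weeks: 2.8 months
- 26 weeks: 3.2 months

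**The case against.** Several counter-arguments have force.

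- **Testing twice may be intended.** The Outcomes section can be read as Bayley at both 12 and 18 months, and it goes on to support testing at more than one age. The 12-month Bayley in Methods sits within routine follow-up. On this reading each infant also has an 18-month score, and the gap is only that neither is named primary. That narrows the point but does not remove it: Table 2 still conflicts with a 12-month outcome test. An analysis plan could rank the two scores, but the protocol passages would still disagree.
- **Differential opportunity to test.** A reader might infer that the 20 extra contacts in the intervention arm let its tests be arranged at different ages. The document does not support this for Bayley. It is given in clinic on follow-up visit days, on a calendar shared by both arms, by a blinded psychologist. AIMS is less tightly tied to visits, but its assessor is blinded too.
- **Many infants judged early.** A reader might infer this from the open window. The share runs from 0% to 100% depending on assumptions that the document does not settle.
- **Power of 61%.** This is a worst case: every infant tested at 12 months and no benefit from the neonatal unit phase. The protocol describes maternal stimulation four times a day in that phase and reports a benefit at 2 years from massage with skin-to-skin care in its own earlier study. Sessions are also instructions for activities done at home daily or three times a week, so benefit need not track the session count.
- **A 12-month comparison is legitimate.** As an as-assigned comparison it is valid, but it evaluates an incomplete programme, and the protocol would have to say so.
- **AIMS wording.** The loose phrase occurs in a description of the instrument. The primary outcome sentences and Table 2 say corrected age, and nothing shows how many infants would change category. One line settles it.

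**Conclusion.** The contradiction is real and concerns the primary endpoint. A 12-month assessment follows at most 8 of 10 sessions and cannot meet Table 2's order, and no passage says whether a 12- or 18-month score is primary. Unequal test age between arms is a conditional risk: it arises if the Table 2 order is enforced in the intervention arm alone.

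The document does not allow the dilution to be sized. The range of about 61% to 71% power rests on a back-solved 0.619 SD, testing of every infant at 12 months, benefit linear in sessions, and an assumed zero to one half of benefit from the neonatal unit phase. It is an illustration, not a forecast. The conclusion rests on the session count and the conflicting passages, not on that range.

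**What to change.** Reconcile the Outcomes section, the Conventional group description and Table 2 as follows.

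- **One primary Bayley-III age.** Use the same corrected age in both arms, by calendar and not conditional on completing sessions. The 18-month visit fits Table 2 and already exists, because follow-up is every 3 months from 12 to 24 months (15, 18, 21, 24).
- **Relation to sessions 9 and 10.** State that these, already placed at 13 to 18 months, are scheduled before the primary assessment. Set a window that does not open before they are due. A symmetric allowance of a month around 18 months would not guarantee this, since session 10 may fall as late as 18 months. Infants who miss a session are still tested at the set age.
- **12-month Bayley.** Make it secondary.
- **AIMS.** Name one scheduled age for the outcome assessment, and read percentiles by corrected age only, as Table 2 does.

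The cost is a protocol amendment, a primary result up to 6 months later and possibly a few more losses to follow-up. No new visits are needed.

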**Fig. 1 Fig1:**
[figure not shown]
Study flow chart. The flow chart of enrolment, allocation, intervention and assessment. *Intervention Group has ten additional appointments for systematic orientation for a continuous global simulation at home and ten home visits

Sample size: the sample size was calculated on the basis of the results of many studies that assessed improvement of motor and mental development or cognitive or language acquisitions. All these studies obtained minimum scores 20% higher after early intervention. For a 5% level of significance and a statistical power of 80%, a sample size of 84 patients will be required to detect a 3-point between-group difference in development scores [20, 24–26]. The allocation of the subjects will be perfomed until the complete calculated sample size based on the number of premature infants who survive until hospital discharge. A number of 20% (number 16) will be added, considering possible loss or death during the follow-up. Total sample size will be 100 preterm infants.

Recruitment: strategies for achieving adequate participant enrolment to reach target sample size will be: to establish a link between the research team and mother and father of each of the subjects included, regardless of the group allocated since randomization. Weekly meetings are performed during NICU stay.

A telephone number is available twenty-four for all questions after discharge and during the follow up. This mobile phone stays each day with a researcher’s member on call to resolve doubts with clarity and security. A prior scheduling of home visits and office appointments is done continuously during the recruitment and assessment according the objectives.

Assignment of interventions: Monitoring the progress of this research is fundamental for assuring that all activities will be achieving stated milestones. The selection of adequate method for generating the randomization sequence is important for result measurements. We have used the research randomizer program available at www.randomizer.org [23].

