To implement a program of continuous and global intervention for preterm infants to be delivered by their families	Improve interaction parental infants since neonatal period with massage therapy by mothers Decrease parental stress Improve neurodevelopment at 12 to 18 months corrected age	During the whole study period. It start one month after receive the grant. There are meetings with the team during the study. All teamneed to be trained to teach the tactile-kinesthetic stimulation by mothers and home visits. The patients are allocated to the study up to a total of 100 (50 in each group) and sequentially randomized when the patients complete 48 h after birth. Exclusion criteria: congenital malformations and parents’refusing to participate in the study. At the end professionals with training to carry out the testings for development assessments will provide the results.
Objective 2:		
Advise and improve the skills of care givers in respect to children’s needs	Reduce to the minimum the lost for follow up (home visits, phone contacts, phone calls) Decrease parental stress that will be measured previously Improve parental infant bonding that will be measured in the beginning Home visits to be sure that the interventions are performed	Patients are randomized to two groups. At admission of the study the intervention will promote a moment of care and further interaction through massage therapy performed by mothers. Following consist of guidelines and measures to promote early intervention with parents’ orientation independently of f the standard evaluation and care that will be performed. There will be daily sessions of 10 to 5 min each one in NICU and three times a week (motor stimulation), daily (cognitive stimulation) at home.
Objective 3:		

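### The primary outcome is a family of at least three scores with no decisive score, age, form or success rule, while the sample size spends a single undivided 5% level

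*Protocol article*

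**What the plan says.** **Which scores.** The Outcomes section of the protocol article describes the primary outcome as a global neurodevelopment evaluation, with infants "evaluated in relation to their motor, and cognitive neurodevelopment using AIMS and Bayley III scales between 12 and 18 months corrected age". That sentence names the motor and cognitive domains only. The Bayley paragraph that follows adds a third domain: "Cognitive, motor, and language development will be considered normal if higher than 89". No global or composite score is defined, and no scale or domain is called decisive.

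**Which age.** The primary-outcome sentence gives a window of 12 to 18 months corrected age. The Bayley paragraph in the same section says the scales "will be used for assessment of neurodevelopment at 12 and 18 months’ corrected age", which reads as two assessments. The description of the conventional group's follow-up, in Methods, places the Bayley at 12 months corrected age for all infants and the AIMS at 6 and 12 months.

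**Which form.** The Sample size paragraph works with score differences: "a sample size of 84 patients will be required to detect a 3-point between-group difference in development scores". Table 2, Objective 3, lists as an outcome the "Number of patients with the Bayley III scale normal for corrected age", with a matching count for AIMS. It also lists statistical measures of the difference between groups, without saying on which variable.

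**Which error level.** The Sample size paragraph gives 5% significance and 80% power, once. The Statistical methods paragraph lists the tests (t, Mann–Whitney, chi-square, Fisher) and gives no hierarchy, no rule that all measures must succeed, and no adjustment.

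**The concern.** A 5% level protects one test of one variable. Here the reader cannot tell which variable, at which age and in which form, decides whether the trial is positive. If several scores are compared and the favourable one may be reported as the primary result, the false positive chance exceeds the stated 5%. If instead all of them had to succeed, the error rate would hold but power would be below 80%. The protocol does not choose between these rules.

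The sample size is affected as well. It was set for one unspecified score at an undivided 5%, so it has no room for a multiplicity adjustment introduced later.

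**Working it through.** **1. The plan's own figure.** Inputs from the Sample size paragraph: 84 evaluable patients, a 3-point difference, 5% (two-sided assumed; the article does not say) and 80% power. Table 2 gives equal arms ("up to a total of 100 (50 in each group"), so 42 per arm after removing the allowance for losses. No SD is given, so the 84 cannot be reproduced directly. It can only be solved backwards:

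- n per arm = 2 (z₀.₉₇₅ + z₀.₈₀)² (SD/3)²
- SD = 3 / [(1.960 + 0.842) × √(2/42)] = 4.91 points
- standardised difference = 3 / 4.91 = 0.61

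The calculation therefore fits one score, tested once at 5%, with an implied SD of 4.91.

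**2. Counting the tests.**

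- Three: AIMS, Bayley motor and Bayley cognitive. This is the strict reading of the primary-outcome sentence.
- Four: the same plus Bayley language.
- Seven: AIMS once and three Bayley domains at 12 and at 18 months, 1 + 3 × 2. Without language this would be 1 + 2 × 2 = 5.

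**3. Chance of at least one false positive, each test at two-sided 5%.** For independent tests this is 1 − 0.95^k:

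- k = 3: 1 − 0.95³ = 14.3%
- k = 4: 1 − 0.95⁴ = 18.5%
- k = 7: 1 − 0.95⁷ = 30.2%

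The scores are positively correlated, but the article gives no correlations. With an assumed equal correlation ρ between the test statistics, the chance is 1 − ∫ φ(u) [Φ((1.96 − √ρ u)/√(1−ρ)) − Φ((−1.96 − √ρ u)/√(1−ρ))]^k du:

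| Tests | Independent | ρ = 0.7 | ρ = 0.9 |
|---|---|---|---|
| 3 | 14.3% | 10.9% | 8.4% |
| 4 | 18.5% | 13.0% | 9.4% |
| 7 | 30.2% | 17.8% | 11.4% |

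These figures do not include the normal/not-normal versions of the same scores.

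**4. What an adjustment would do to the planned size.** At the implied SD and 42 per arm, power is Φ(2.802 − z₁₋α/₂):

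- α = 0.05: Φ(2.802 − 1.960) = 80%
- α = 0.025 (first Holm step, two primaries): Φ(2.802 − 2.241) = 71%; 80% would need about 102 evaluable
- α = 0.0125 (Bonferroni, four scores): 62%; 80% would need about 120 evaluable

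The planned total of 100 already includes 16 for loss or death, so it does not supply these numbers.

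**The case against.** **Multiplicity may sit in an analysis plan that is not shown.** This is fair as far as the adjustment method goes, and its absence from a condensed article is not a finding. But which variable is primary, in what form and at what age fixes the sample size and belongs in the protocol. On age and form the article does speak, and it disagrees with itself.

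**Testing each score at 5% is not stated.** This stands. The only 5% is the sample-size input. The inflation figures hold only if any single success would be claimed.

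**The count can be overstated.** This also stands. A reader might infer at least four primary scores, all at two ages, making eight tests and an error of 1 − 0.95⁸ = 34%. The article does not support that. Language is absent from the primary-outcome sentence, and AIMS is never set at both 12 and 18 months. The two-age reading of the Bayley rests on one phrase, against a window elsewhere and 12 months in the follow-up description. Seven tests is the upper count at two ages.

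**The counts of normal infants may only be a summary.** This is possible, because the same cell of Table 2 also lists statistical differences between groups. A reader might also want to put a figure on the power lost by dichotomising. That needs an SD, a control mean and a shift that the article does not give, and such a figure would not describe its 3-point target.

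**Using both instruments is clinically sensible.** The article argues for combining AIMS and Bayley because false positives on single assessments are common. That supports measuring both. It does not settle which one decides the trial.

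**Conclusion.** The concern holds. The primary outcome is a family of at least three scores with no composite, decisive score or success rule. Its Bayley age is inconsistent between and within sections, and its form differs between the Sample size paragraph and Table 2. One undivided 5% level was used to size the trial.

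If any single success would count, the false positive chance is about 8–14% for three scores, 9–19% for four and 11–30% for seven tests. That is roughly 1.7 to 6 times the stated level (8.4/5 to 30.2/5). The ranges rest on assumed correlations from 0.9 down to zero and on two-sided tests. If all measures had to succeed, there would be no inflation, and the cost would be power. The article leaves the choice open, and that omission is the defect whichever rule was intended.

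**What to change.** Before unblinding, by dated amendment carried through to the registry entry:

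1. Name one primary variable, as a continuous score at one fixed corrected age with a stated visit window. Alternatively name at most two, for example the Bayley-III cognitive and motor composites, which match the stated motor and cognitive aims, tested by Holm at an overall two-sided 5%. Which score to promote is the sponsor's choice.
2. Make the remaining scores, the other age and all normal/abnormal categories secondary.
3. Reconcile the follow-up description, the Outcomes section, the Sample size paragraph and Table 2 on age and form, and state in the sample size which score the 3 points refer to.

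**Cost.** Mainly wording and an amendment. The article says recruitment and data collection are continuing and that data analysts and outcome assessors will be blinded, so the choice can still be made without knowledge of results. A single primary loses no power. With two, power at the first Holm step falls from 80% to about 71% at the effect size implied by 84 evaluable patients; keeping 80% there would take about 102.
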